### Primary aims: HIV/AIDS and HIV testing knowledge acquisition and retention (information)

Determine how (Aim 1) short-term improvement and (Aim 2) longer-term retention of HIV/AIDS and HIV testing knowledge varies by information delivery mode (pictorial brochure or video), language (English or Spanish) and health literacy level (lower or higher) per four alternative hypotheses (HAs) (also provided are examples of outcomes of each HA):HA1 (3-way interaction of information delivery mode, language, and health literacy): e.g., improvement and/or retention of knowledge will be greatest among participants in the video arm who are English speakers and have higher health literacy, and will be least among those in the pictorial brochure arm who are Spanish speakers and have lower health literacyHA2 (2-way interaction of information delivery mode with language or health literacy): e.g., improvement and/or retention of knowledge will be greatest among participants in the video arm who are English speakers or higher health literacy patients, and will be least among those in the pictorial brochure arm who are Spanish speakers or lower health literacy patientsHA3 (no interaction with information delivery mode): e.g., improvement and/or retention of knowledge will be greater in the video arm than the pictorial brochure arm regardless of language and health literacy levelHA4 (no difference): improvement and/or retention of knowledge will be the same regardless of information delivery mode, language, and health literacy level (i.e., either a pictorial brochure or a video is useful for all patients)

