#### Primary aims analysis

For Aim 1, we expect that HIV/AIDS and HIV testing knowledge scores can be reasonably approximated by a normal distribution (Table 4). We will compare differences in pre- vs. post- changes in scores between information delivery modes by paired t-tests. If the data are not normally distributed, we will use signed-rank tests. All tests will be executed on an intention-to-treat basis (non-adherence to assigned information delivery mode likely is minimal). Comparisons will first be made for each stratum. MANOVA/ANCOVA will be used for combined samples where language and literacy level are used as stratifying (main) factors. To further account for baseline covariates (e.g., demographic characteristics), a generalized linear mixed-effect model will be fit to the data. The parameters of interest are the coefficients of the dummy variable indicator of study arm assignment and its interactions with language and health literacy level.

**Table 4 Tab4:** Analyses of primary aims

Primary aims	Measurements	Analytic methods
Aim 1. Short-term improvement in HIV/AIDS and HIV testing knowledge **HA1**: 3-way interaction (mode*language*literacy level) **HA2**: 2-way interaction (mode*language or literacy level) **HA3**: no interaction (difference by mode only) **HA4**: no difference	HIV/AIDS and HIV testing knowledge questionnaire at baseline in ED at time of HIV testing, post- vs. pre-information delivery	• Paired t-tests • Signed-rank tests • MANOVA/ANCOVA • Generalized linear mixed-effects regression
Aim 2. Retention of HIV/AIDS and HIV testing knowledge at 3, 6, 9, and 12 months **HA1**: 3-way interaction (mode*language*literacy level) **HA2**: 2-way interaction (mode*language or literacy level) **HA3**: no interaction (difference by mode only) **HA4**: no difference	HIV/AIDS and HIV testing knowledge questionnaire at 3, 6, 9, and 12 months vs. baseline (post-information delivery)	• Paired t-test for each follow-up vs. baseline • Linear mixed-effects regression (assuming constant degradation over time) • Broken-stick linear mixed-effects regression (for non-constant degradation over time)

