The generalized linear mixed-effect model will be structured as follows: *Y*^***^_*ij*_ *= α*_*j*_ *+ f(R*_*i*_*,LG*_*i*_*,LT*_*i*_*; β) +* μ_i_ *+ θX*_*i*_*,* where *j = 0,1* indicates pre- and post-information, *Y*^***^_*ij*_ is the outcome of subject *i*, R_i_ indicates the arm assignment, *α*_*j*_ is the intercept (*α*_*0*_ being the pre-information value for j = 0; and *α*_*1*_ the post-information value for j = 1), *β* is a vector that captures the main effects, and 2- and 3-way interactions among information delivery mode *(R),* language *(LG*), and literacy *(LT)*, *f* () is a linear predictor function, and *X*_*i*_ contains important or stratification covariates, with *θ*θ being their effects. For this unified approach, *Y*_*ij*_^***^ = *g*[E (*Y*_*ij*_)] where *g*() is an appropriate transformation of the outcome being analyzed. For example, for continuous outcomes, *g*() can be an identify link; for count or binary outcomes (as in the exploratory aims), *g*() can be a log or logit/probit transformation. We will assume that *u*_*i*_
*~ N(0, τ*^*2*^*)*, which is a random effect that captures the within-subject correlation of the repeated measurements. We will fit the models using the restricted maximum likelihood method, or generalized estimating equations (GEE) if non-identify links are used.

For Aim 2, we will first compare the baseline literacy scores at each of the follow-up visits to the baseline score (post-information delivery) using paired *t*-tests. If the retention of HIV/AIDS and HIV testing knowledge demonstrates a linear trend over time, we will fit a linear mixed-effect model to the combined data, in which independent variables will include time, information delivery mode, language and baseline health literacy level; their interactions; age, gender, etc. If the trend is not linear, we will consider fitting a broken-stick (piecewise linear) linear mixed-effect model. The parameters of interests are the coefficients of time, indicating follow-up assessments, and the interactions of time and study arm assignment, information delivery mode and language.

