If a linear assumption is supported by data, the linear predictor in the above model will be expressed as *α*_*0*_ *+ β*_*1*_*[time] + β*_*2*_*[time]*R*_*i*_*[mode]*, where *β*_*1*_ and *β*_*2*_ capture HIV/AIDS and HIV testing knowledge retention rate over time and the difference in the rate between two delivery modes. We will further evaluate the 2- and 3-way interactions *β*_*2*_*[time]*[language]*R*_*i*_
*[mode]* and *β*_*2*_*[time]*[health literacy level]*R*_*i*_*[mode]* and possibly (if data allow) 4-way interactions *β*_*2*_*[time]*[language]*[health literacy level]*R*_*i*_*[mode]*, to investigate the interaction of information delivery mode with language and health literacy and whether one delivery model works better in certain sub-groups. Our analysis by time will permit us to determine if and when HIV/AIDS and HIV testing knowledge degrades, and if and when knowledge reaches baseline pre-information levels (i.e., before an intervention), which would suggest a need for repeat delivery of this information at subsequent HIV testing encounters within 12 months. We also will determine if degradation varies by information delivery mode, language, and health literacy level. We recognized that there is no established minimum standard for what level of HIV/AIDS and HIV testing knowledge is necessary or desired; however, we believe that it should be at least greater than pre-information knowledge levels, and will plan the analyses accordingly.

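### Aim 1 mixed model: the named arm and two-way coefficients depend on an unstated coding of language and literacy; contrasts averaged over strata would test HA2 with more power at no cost

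*Protocol article*

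**What the plan says.** All places are in the protocol article.

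- **Aim 1 target (Primary aims analysis).** After the mixed model is introduced, the parameters of interest are named as the "coefficients of the dummy variable indicator of study arm assignment and its interactions with language and health literacy level".
- **Aim 1 model (same section).** The vector β "captures the main effects, and 2- and 3-way interactions among information delivery mode", language and literacy. Only the arm is called a dummy variable. No coding is given for language or literacy, and no contrast averaged over strata is named.
- **Other Aim 1 analyses (same section).** "Comparisons will first be made for each stratum". Then: "MANOVA/ANCOVA will be used for combined samples where language and literacy level are used as stratifying (main) factors". The mixed model follows, to bring in baseline covariates. Table 4 lists all of these methods against HA1 to HA4 without saying which one decides each hypothesis.
- **HA3 (Primary aims).** It is labelled as the case without interaction with delivery mode, for example that "improvement and/or retention of knowledge will be greater in the video arm than the pictorial brochure arm regardless of language" and literacy.
- **Aim 2 (Primary aims analysis).** The linear predictor first contains only time and time by mode, whose coefficients "capture HIV/AIDS and HIV testing knowledge retention rate over time and the difference in the rate between two delivery modes". Interactions with language and literacy are evaluated after that.

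**The concern.** In a model with all interactions, a lower-order coefficient has no meaning until the coding of the other factors is known. If language and literacy are entered as 0/1, the arm coefficient is the mode difference in one of the four language-by-literacy strata. The mode-by-language coefficient is the interaction at one literacy level, and the mode-by-literacy coefficient is the interaction at one language. If the factors are centred, the same terms are averages over strata.

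Two things are at stake. The first is precision: under 0/1 coding the two-way terms use half of the participants and the arm term a quarter. The second is stability: where interactions exist, the reported coefficients can change with an arbitrary choice of reference category. HA2 is most exposed, because two-way interactions have less power to spare than the overall mode difference.

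**Working it through.** **Inputs.** From Table 3, Aim 1: SD 3; within-person correlation 0.7; minimum 125 per cell (8 × 125 = 1000) and final 150 per cell (8 × 150 = 1200); mode effect 1.5; two-way effect size built as 1.5 + 0.75 = 2.25; three-way as 1.5 + 0.75 + 0.75 = 3.0. Two-sided α is 0.05. The 0.75 is read as the interaction itself, meaning the amount by which the mode effect differs between two levels of a factor.

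**The plan's own power figures.** Table 3 states 0.80, 0.97 and 0.99 for HA1, HA2 and HA3 at 125 per cell. With change-score SD 2.324 and effects 3.0, 2.25 and 1.5, all three powers come out at 0.999 or more. Two other readings come within two points of all three stated figures:

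- SD adjusted for baseline, 3√(1 − 0.49) = 2.142, effect 1.5 for all three, reference-cell standard errors: 0.790, 0.975, 0.9998.
- SD of an uncorrelated change, 3√2 = 4.243, effects 3.0, 2.25 and 1.5, averaged standard errors: 0.798, 0.987, 0.9999.

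One reading uses reference-cell coefficients and the other uses averages, so the power table does not show which was intended.

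**Standard errors.** σ = 3√(2(1 − 0.7)) = 2.324 for a change score, with n per cell in a balanced 2×2×2 layout.

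| Term | 0/1 coding | n = 125 | Averaged over strata | n = 125 |
|---|---|---|---|---|
| Arm | σ√(2/n) | 0.294 | σ√(0.5/n) | 0.147 |
| Arm by one factor | σ√(4/n) | 0.416 | σ√(2/n) | 0.294 |
| Three-way | σ√(8/n) | 0.588 | σ√(8/n) | 0.588 |

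The ratios (2, √2 and 1) depend only on the design, not on σ.

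**Power, Φ(δ/SE − 1.96).**

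- HA2, δ = 0.75, n = 125: 0.75/0.416 gives 0.44; 0.75/0.294 gives 0.72.
- HA2, δ = 0.75, n = 150: the standard errors are 2.324√(4/150) = 0.379 and 2.324√(2/150) = 0.268, giving 0.51 and 0.80.
- HA2 with other SDs, δ = 0.75, n = 125: 0.50 against 0.79 at SD 2.142; 0.29 against 0.51 at SD 3.
- HA2 if the interaction itself were 2.25, n = 125: at least 0.999 either way, so nothing is lost.
- HA3, δ = 1.5, n = 125: 0.999 against more than 0.9999.

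**Dependence on the reference stratum.**

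- *No interaction, mode effect 1.5 everywhere.* The arm coefficient is 1.5 under every coding.
- *Mode by language only, 1.5 in one language and 2.25 in the other.* The arm coefficient is 1.5 or 2.25 by reference; the average is (1.5 + 2.25)/2 = 1.875. The two-way coefficient is 0.75 in size throughout.
- *3.0 in English speakers with higher literacy, 1.5 in the other three strata.* The arm coefficient is 1.5 or 3.0; the average is (3 × 1.5 + 3.0)/4 = 1.875. The mode-by-language coefficient is 0 when lower literacy is the reference, and +1.5 or −1.5 when higher literacy is; the average is 0.75. The three-way coefficient is 1.5 in size throughout.

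So the arm term moves with the reference when any interaction with mode exists, and the two-way terms change in size only when there is a three-way interaction.

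**The case against.** The strongest reply is that the difficulty presupposes 0/1 coding of language and literacy, which the article never states. Centred coding removes it, describing β as holding main effects fits that reading, and coding is commonly left to an analysis plan. It is true that 0/1 coding is an inference. What remains is that the article does fix its parameters of interest, and fixes them as coefficients whose meaning turns on that coding.

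A reader might go further and infer that HA3 and HA2 are tested only on part of the sample. The documents do not support that. The same section plans comparisons within each stratum and a MANOVA/ANCOVA on the combined sample, which gives a whole-sample comparison by mode. HA3 is also defined as the no-interaction case, in which the arm coefficient is the same for every reference stratum.

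A reader might also infer that Aim 2 has the same fault. It does not as written: β₂ enters a predictor without language or literacy terms, so it is first a whole-sample difference in slope. The question arises only once the interactions are added.

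Finally, the standard errors above are those of a change-score analysis, whereas the article models pre and post scores jointly. That limits the absolute power values, but not the standard-error ratios of a balanced design.

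**Conclusion.** The point holds as a free improvement to the Aim 1 mixed model. Unless language and literacy are centred, the named arm coefficient describes one stratum, and each named two-way coefficient describes one level of the other factor. The practical loss is mainly in HA2: for a 0.75-point interaction, power is 0.44 instead of 0.72 at 125 per cell, or 0.51 instead of 0.80 at 150. This rests on Table 3's SD and correlation, a change-score calculation, balanced cells, 0/1 coding, and reading 0.75 as the interaction. HA1 is unaffected apart from sign. HA3 at 1.5 points loses no material power; its standard error doubles, which matters for the width of its interval.

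**What to change.** In Primary aims analysis, replace the sentence that names the Aim 1 parameters with wording such as: HA3 is tested by the video-brochure difference averaged with equal weight over the four language-by-literacy strata; HA2 by the mode-by-language and mode-by-literacy contrasts, each averaged over the other factor; HA1 by the three-way contrast. Obtain these by coding the three factors as −1/2 and +1/2, or as marginal contrasts from the same fitted model. Report the stratum-specific differences alongside, so that an average does not hide effects that differ.

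For Aim 2, add only that the overall retention difference is taken from the model before the language and literacy interactions enter, or as a marginal contrast once they have.

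The cost is a few lines of text and one coding statement. No data, sample size or test of HA1 changes.

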#### Information delivery and post-information delivery questionnaires

We will randomly assign patients in a 1:1 ratio into information delivery mode Arm 1 or Arm 2. As noted previously, the two arms will be stratified within language (English or Spanish) and health literacy level [22] (lower vs. higher) (*n* = 150/stratum). We will use block randomization techniques to ensure that there are equal numbers in each arm per study site and stratum using a centralized, random assignment computerized system. Randomization sequences by language and health literacy level will be posted on a secure website that RAs across all four sites will consult when assigning participants to study arms. The advantage of this approach is that we can monitor enrollment and balance within study arms and across study sites easily, address concerns as they arise, and permit efficient use of study resources. The two groups will differ by the following:Arm (1): HIV/AIDS and HIV testing video: Participants in Arm 1 will watch the video, “What do you know about HIV and HIV testing?” (in English or Spanish) on a tablet computer in the ED while the RA waits. They will listen to the audio components using disposable headphones.Arm (2): HIV/AIDS and HIV testing pictorial brochure: Participants in Arm 2 will be provided with a copy of our HIV/AIDS and HIV testing pictorial brochure (in English or Spanish) to review in the ED. Arm 2 participants will read the brochure while the RA waits. The RAs will not provide clarifications or assistance with the information in the pictorial brochure.

After watching the video or reviewing the pictorial brochure, all patients will complete the post-information questionnaires using the automated telephone key-pad response system (the HIV risk self-perception and value of HIV testing, HIV/AIDS and HIV testing information delivery mode preferences and satisfaction, the HIV/AIDS and HIV testing knowledge, and the HIV risk-taking questionnaires). Patients will receive a re-chargeable gift card for participating.

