#### Sample size considerations

The study sample size is *n* = 1200, with equal size strata (*n* = 150) by language, health literacy level, and information delivery mode (Fig. 4). This sample size is based on a 2x2x2 full factorial design and will satisfy the requirements for analysis of the two primary aims and the four alternative hypotheses paired with each aim. The minimum sample size is calculated for a power of 0.80 and a two-sided *α = 0.05* level of significance (Table 3). In general, a larger sample size is needed for greater variation of scores within study arms and strata, lower within-person correlations of scores, and higher loss-to-follow-up. To maximize power, we chose conservative values based upon our prior studies. We increased the sample size by 20% to account for the heterogeneity in patients among the four study sites, and by a conservative additional 25% to account for possible attrition. Based upon other 12-month ED intervention follow-up studies [10], HIV/STD testing studies [57–59], and studies conducted at our own ED [60, 61], a 25% attrition rate at 12 months likely is a worst-case scenario. We expect that our experience and enhanced measures to encourage and facilitate follow-up will result in higher follow-up rates. As of publication of this manuscript, 1165 participants enrolled completed the three-month follow-up.

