Aim 2. Retention of HIV/AIDS and HIV testing knowledge at 3, 6, 9, and 12 months ** HA1**: 3-way interaction (mode*language*literacy level) ** HA2**: 2-way interaction (mode*language or literacy level) **HA3**: no interaction (difference by mode only) ** HA4**: no difference	**100** This **minimum** sample size by stratum will yield a power of 0.80, 0.97 and 0.99 for testing HA1, HA2, and HA3, versus HA4 (as the NULL)	**800** After adding 25% to account for loss-to-follow-up and 20% for heterogeneity among study sites, the **final sample** size is **1200** = 800*(1 + 25%)*(1 + 20%)	• Long-term within-person correlation is 0.4 or higher • The scores on the knowledge questionnaire in the pictorial brochure arm will degrade to the pre-information baseline level with an average drop of 2 points by 12 months. The score in the video information arm will degrade by an average drop of 1 point. So, compared to baseline, the difference (effect size) in long-term retention of information in the video arm as compared to the pictorial brochure arm is Δ = (3.5–1)-(2–2) = 2.5. • We will assume a similar effect size for 2- and 3-way interactions

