### Study analysis (begins at end of recruitment month 43)

#### Enrollment summary and comparison of participants at baseline

We will report on participant enrollment and summarize the reasons for accepting or declining enrollment or drop-out from the study using the Consolidated Standards of Reporting Trials (CONSORT) approach [62]. We will summarize the demographic characteristics, HIV testing history, and health literacy level (measured by the SAHL-S&E [22] and brief instruments) using conventional statistics, such as means/standard deviations, medians/ranges, or counts/frequencies with corresponding 95% confidence intervals (CIs), as appropriate. For Latino participants, we will summarize nativity and US acculturation (measured by the SASH [63, 64]) in a similar manner. We will summarize these baseline characteristics for all participants and as stratified by informational delivery mode (pictorial brochure or video), language preference (English or Spanish), and health literacy level (lower or higher). Next, we will compare the baseline characteristics of study participants between the study arms using Pearson’s Χ^2^ or Fisher’s exact test for categorical variables and Student’s t-test for normally distributed or Wilcoxon’s rank-sum test for non-normally distributed continuous variables to assess the success of the randomization procedure. Any chance imbalances between the two arms will be documented and investigated, and will be adjusted for by including the imbalanced covariate as an independent variable in our subsequent regression analyses, or through a weighted analysis using a propensity score (propensity to be enrolled in the study with weights equal to the inverse of the propensity score) [65]. A two-tailed, *α = 0.05* significance level will be used for all analyses.

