#### Secondary analyses of primary aims

Our a priori secondary analyses entail examining if there are sub-groups with differences in HIV/AIDS and HIV testing knowledge improvement or retention in the short- and longer-term. We will assess the impact of demographic characteristics, HIV testing history, and testing site for all participants, as well as nativity and US acculturation for Latino participants in these secondary analyses. For these secondary analyses, we will use the aforementioned generalized linear mixed-effect models to take into account the two-arm clinical trial design; language and health literacy level; the repeated measures, the longitudinal data that are collected at baseline and follow-up assessments; and the covariates of interest (e.g., demographic characteristics and HIV testing history). Our focus of analysis will be the main effects of the covariates of interest and their interaction effects with study arm, stratifying factors and time. For longer-term retention of knowledge, we also will examine the impact of repeated testing during the follow-up period.

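### The Aim 2 retention model leaves out the pre-information knowledge score and refers to a post-randomisation score, although Table 3 powers the gain over the pre-information level

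*Protocol article*

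**What the plan says.** **Model.** Under Primary aims analysis, the Aim 2 mixed model is described so: "independent variables will include time, information delivery mode, language and baseline health literacy level; their interactions; age, gender, etc". The linear predictor is then given as an intercept, a time term (β1) and a time-by-mode term (β2). β2 is the difference between modes in the rate at which knowledge is retained, and interactions with language and health literacy follow.

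**Reference score.** Table 4 gives the Aim 2 measurement as "HIV/AIDS and HIV testing knowledge questionnaire at 3, 6, 9, and 12 months vs. baseline (post-information delivery"), and the text applies paired t-tests against that same score. It is taken after the video or brochure, so after randomisation.

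**Pre-information score.** The 25-item questionnaire is also completed before information delivery (Table 2; Pre-information delivery questionnaires). In Aim 2 this score serves only as a level to which knowledge may fall back. The baseline characteristics listed for the imbalance check are demographics, testing history and health literacy, so that route would not bring it in.

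**Sample size.** Table 3 defines the Aim 2 effect relative to the pre-information level: (3.5 − 1) − (2 − 2) = 2.5 points at 12 months. It assumes that "Long-term within-person correlation is 0.4 or higher" and states that the minimum "sample size by stratum will yield a power of 0.80, 0.97 and 0.99 for testing HA1, HA2, and HA3".

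**Site.** Block randomisation is to "ensure that there are equal numbers in each arm per study site and stratum". The Aim 2 list does not name site. Secondary analyses of primary aims does: "We will assess the impact of demographic characteristics, HIV testing history, and testing site for all participants".

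**The concern.** A baseline value of the outcome is usually among the strongest predictors of its later values. Leaving it out does not bias a randomised comparison. It does leave predictable variation in the error term, and it leaves any chance difference in initial knowledge in a comparison of 12-month levels.

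The post-information score cannot take its place as a neutral baseline, because the delivery mode is expected to change it. Measured from that score, Table 3's own figures (a drop of 2 points with the brochure, 1 with the video) make the arms differ by 2 − 1 = 1 point. Measured from the pre-information score they differ by 2.5 points. The quantity that was powered and the quantity that Table 4 measures are therefore not the same.

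HA1, the three-way interaction, has the least margin of the Aim 2 hypotheses and bears on whether information should be tailored. Precision matters most there.

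**Working it through.** **Inputs.** SD about 3 (Table 3, Aim 1 row); long-term correlation 0.4 and Aim 2 effect 2.5 points, similar for interactions (Table 3, Aim 2 row); pre-to-post correlation 0.7 (Aim 1 row); minimum 100 per stratum. Sample size considerations: "The minimum sample size is calculated for a power of 0.80 and a two-sided" 0.05 level. The same two-tailed 0.05 "significance level will be used for all analyses". Assumption: 0.4 applies between the pre-information score and each follow-up score.

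**Variance of one participant's 12-month quantity**

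- Follow-up score alone: 3² = 9 (SD 3.000)
- Follow-up score adjusted for the pre-information score: 9 × (1 − 0.4²) = 7.56 (SD 2.750)
- Change from an earlier score at correlation 0.4: 2 × 9 × (1 − 0.4) = 10.8 (SD 3.286)

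**The plan's own powers.** Power = Φ(2.5/SE − 1.960), with SE = SD × √(8/100) for the three-way contrast (HA1) and SD × √(4/100) for a two-way contrast in four cells (HA2).

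| Analysis | HA1 | HA2 | HA3 |
|---|---|---|---|
| Stated in Table 3 | 0.80 | 0.97 | 0.99 |
| Change from pre-information | 0.767 | 0.967 | >0.99 |
| 12-month score alone | 0.838 | 0.986 | >0.99 |
| 12-month score adjusted for pre-information | 0.895 | 0.995 | >0.99 |

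The change score reproduces HA2 and agrees with HA3. No row gives exactly 0.80 for HA1. The size arithmetic does reproduce: 800 × 1.25 × 1.20 = 1200.

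**Gain on a single 12-month score.** The variance falls by 1 − 7.56/9 = 16%. From a power of 0.80, z = 1.960 + 0.842 = 2.802. Then 2.802 × √(9/7.56) = 3.057, and Φ(3.057 − 1.960) = 0.864. On Table 3's inputs for HA1 the step is 0.838 to 0.895.

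**Gain on change from the post-information score.** The covariance of that change with the pre-information score is 9 × (0.4 − 0.7) = −2.7. The variance becomes 10.8 − 2.7²/9 = 9.99, a cut of 7.5%. Φ(2.802 × √(10.8/9.99) − 1.960) = 0.830, so about 3 points.

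**Gain in the repeated-measures model.** These are generalised least squares variances with visits at 0 (post-information), 3, 6, 9 and 12 months.

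- *Arm difference at 12 months:* 0.80 rises to between 0.86 and 0.88, with correlations of 0.4 to 0.6 among the scores from post-information onward.
- *Slope difference β2, all plan correlations (0.7 short-term, 0.4 long-term):* 0.825 with a separate intercept for each arm, 0.819 with one common intercept. With 0.4 throughout and separate intercepts there is no gain. A simulated random-intercept model gave the same standard error (0.0173) with and without the score.
- *Slope difference β2, other correlations:* 0.839 if the scores from post-information onward correlate at 0.6 (pre-to-post 0.7, separate intercepts), and 0.849 with 0.4 throughout and a common intercept.

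**HA2 and HA3.** Starting from the stated 0.97 and 0.99, the same 16% variance cut gives 0.987 and 0.997.

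**The case against.** The main objection is that β2 is the named Aim 2 parameter, and a covariate that is constant over time hardly affects a within-person slope. This stands: for β2 the gain is small or nil. Moving to a 12-month level would change the target, and the plan does ask whether and when knowledge degrades, so β2 should stay. But Table 3 powers a 12-month difference from the pre-information level, so reporting that difference as well uses the plan's own quantity.

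A second objection is that the list is open-ended and a journal article condenses. Nothing forbids the covariate. Yet the article does write out the model, its reference score and its parameters, and an open ending after age and gender does not commit the analysis to the baseline outcome.

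Three stronger readings are tempting and are not supported:

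- *A loss of about 12 power points.* The step from 0.80 to 0.918 compares variance 10.8 with 7.56, that is, change from the pre-information score with adjustment for it. The change score already uses that score, so the step is not the cost of leaving it out.
- *Large gains for small interactions.* Illustrations with a 0.75-point interaction borrow the Aim 1 increment. For Aim 2, Table 3 assumes interactions similar to the 2.5-point effect.
- *Site is excluded.* The general model's covariate term X allows for stratification factors, the Aim 2 predictor is written as part of that model, and the list is open. Site is permitted but not named. Reading Table 3's 20% inflation as removable between-site variance would be an assumption, so no power figure is attached to site.

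**Conclusion.** The point holds at modest size. The Aim 2 model as written does not include the only pre-randomisation measure of the primary outcome, and its reference score is post-randomisation and differs from the one on which Aim 2 was sized.

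Including the pre-information score is worth about 6 points for the 12-month mode contrast (0.80 to 0.86; HA1 on Table 3's inputs, 0.84 to 0.90), and up to about 8 points in the repeated-measures version. It is worth about 3 points for change from the post-information score and about 0 to 3 points for β2 on the plan's correlations (up to 5 under the other structures tried). For HA2 and HA3 it is negligible.

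These figures rest on SD 3, correlation 0.4 between the pre-information and each follow-up score, and a normal approximation. A higher correlation would raise the gain on the 12-month score. The issue is precision and consistency of the target, not validity.

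**What to change.** In the Aim 2 mixed model, add the pre-information knowledge score and its interaction with visit. Report the adjusted mode difference at 12 months, with its interactions with language and health literacy, as the quantity that Table 3 powers. Keep β2 as the planned degradation-rate contrast beside it, and keep the paired comparisons with the post-information score as a description of forgetting within arms. State that the covariate term X in the Aim 2 model includes study site, since randomisation is balanced on it; this is a clarification.

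Only analysis wording changes. All variables are already collected, and the cost is a few degrees of freedom among about 1200 × 0.75 = 900 participants at 12 months. Fixing the covariates now also avoids choosing them after seeing imbalance.
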